**FIGURE 1 F1:**
[figure not shown]
Flow diagram of the study design.

**TABLE 1 T1:** Schedule of enrolment, assessments, and data collection.

Period	Enrolment/Baseline	Allocation	Treatment period			Follow-up period
Time points	Introduction period	0week	4 weeks	8 weeks	12 weeks	48weeks
Eligibility screening	×	—	—	—	—	—
Informed consent	×	—	—	—	—	—
Physical Examination	×	×	—	—	—	—
Characteristic	×		—	—	—	—
Random allocation	—	×	—	—	—	—
Interventions	—	—	×	×	×	—
Clinical Assessments	—	—	×	×	×	—
Medical history	×	×	×	×	×	×
Body weight	×	×	×	×	×	—
Waist circumference	×	×	×	×	×	—
Body mass index	×	×	×	×	×	—
Electrocardiogram	—	×	—	—	×	—
Routine urinalysis	—	×	—	—	×	—
Complete blood count analysis	—	×	—	—	×	—
HbA1c	—	×	—	—	×	×
FPG	×	×	×	×	×	×
2 h-PG	×	×	—	—	×	×
Blood lipid indicators	×	×	—	—	×	×
TCM symptom score	×	×	×	×	×	×
Liver and kidney function	—	×	×	×	×	—
Islet function	—	×	—	—	×	×
Urinary microalbumin	—	—	—	—	—	×
Urinary microalbumin/-creatinine ratio	—	—	—	—	—	×
Cardiac ultrasound	—	—	—	—	—	×
Carotid artery ultrasound	—	—	—	—	—	×
Biological specimens	—	×	—	—	×	—
Adverse event	—	×	×	×	×	—

FPG, fasting plasma glucose; PG, plasma glucose; TCM, traditional Chinese medicine.

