### Adverse Events

AEs will be continuously monitored during the 12-week treatment period and during the 36-week follow-up period. AEs indexes will include electrocardiogram findings, hepatic function tests (i.e., levels of alkaline phosphatase, aspartate aminotransferase, alanine aminotransferase, and g-glutamyl-transpeptidase), renal function tests (i.e., creatinine and urea levels), complete blood count analysis, routine urinalysis, islet function, urinary microalbumin, urinary microalbumin/creatinine ratio, cardiac ultrasound, and carotid artery ultrasound. In addition, AEs in the form of uncomfortable symptoms and other ailments will be comprehensively documented, including the timing of onset, severity, duration, treatment, and outcomes. Each AE associated with the intervention drugs will be classified as mild, moderate, or severe. Severe AEs will be submitted to the principal investigator and ethics committee within 24 h of onset. All AEs will be resolved properly. The Guang’anmen Hospital will cover non-negligent harm associated with the protocol. The AE severity evaluation criteria are as follows: 1) Mild: the patients can tolerate the discomfort, which does not interfere with the treatment, does not require special treatment or affect patient rehabilitation; 2) Moderate: the patients cannot tolerate the discomfort and require special treatment, which may affect their recovery outcomes; and 3) Severe: the patients are at risk of death or disability and require immediate emergency treatment.

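### The mild and moderate adverse-event grades turn on tolerance of discomfort and offer no criterion for the laboratory, ECG and imaging findings listed as AE indexes, so some non-emergency events fit no grade and have no route to the 24-h report

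*Protocol article*

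**What the plan says.** All the relevant text is in the Adverse Events section of the protocol article. The list of what is monitored begins "AEs indexes will include electrocardiogram findings, hepatic function tests" and continues with renal tests, blood count, urinalysis, islet function, urinary microalbumin, its ratio to creatinine, and cardiac and carotid ultrasound. The next sentence adds symptoms: "In addition, AEs in the form of uncomfortable symptoms and other ailments will be comprehensively documented".

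The grading rule applies to drug-related events: "Each AE associated with the intervention drugs will be classified as mild, moderate, or severe". The three definitions are printed in full:

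- "Mild: the patients can tolerate the discomfort, which does not interfere with the treatment, does not require special treatment or affect patient rehabilitation"
- "Moderate: the patients cannot tolerate the discomfort and require special treatment, which may affect their recovery outcomes"
- "Severe: the patients are at risk of death or disability and require immediate emergency treatment"

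Events graded severe must reach the principal investigator and the ethics committee inside 24 h. The section gives no other expedited route. In Table 1 the row "Liver and kidney function" is marked at weeks 0, 4, 8 and 12. ECG, urinalysis and blood count are marked at weeks 0 and 12 only.

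**The concern.** The scale suits complaints that a patient can describe. It does not suit the indexes named just before it, which are read from an analyser, a tracing or a scan and may be abnormal in a patient who feels well. An investigator facing a clearly abnormal liver or kidney result in such a patient has no discomfort to judge, and no grade mentions the size of the abnormality.

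Two things depend on the grade. It decides which events are escalated within 24 h, and it is the severity that will be recorded for each drug-related event. Where the definitions do not settle the grade, the investigator's judgement does. The trial is open-label, and the section on test drugs and blinding promises blinding for efficacy assessment and for analysis without mentioning AE grading. Similar events could then be graded differently by different investigators, possibly with the arm known.

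**Working it through.** No arithmetic applies; the check is to read each definition as a set of conditions.

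- **Mild:** discomfort is tolerable, and there is no interference with treatment, no special treatment and no effect on rehabilitation.
- **Moderate:** discomfort is not tolerable, and special treatment is required.
- **Severe:** risk of death or disability, and immediate emergency treatment is required. Discomfort is not mentioned.

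For events that are not emergencies, severe is excluded. Crossing the two remaining conditions gives:

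| | No special treatment needed | Special treatment needed |
|---|---|---|
| Tolerated or symptom-free | Mild, if treatment and rehabilitation are unaffected | No grade: fails mild (treated) and moderate (tolerated) |
| Not tolerated | No grade: fails mild (not tolerated) and moderate (untreated) | Moderate |

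The upper right cell is the one that matters for the listed indexes. A symptom-free laboratory or ECG abnormality that needs special treatment but is not an emergency falls there. The lower left cell is also empty, but it concerns symptoms and not the indexes.

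In the upper left cell, a symptom-free abnormality is mild if absence of discomfort is read as tolerable discomfort. If the wording is read strictly, it has no grade. On either reading it cannot rise above mild, because no condition refers to the size of the value.

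Comparing the scale with the index list: there are ten index groups (ECG, hepatic, renal, blood count, urinalysis, islet function, microalbumin, microalbumin/creatinine ratio, cardiac ultrasound, carotid ultrasound). None of the ten has a criterion in any of the three grades.

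For reporting, the 24-h rule is attached to severe alone. A symptom-free abnormality that puts the patient at risk of death or disability and needs emergency treatment is severe and is reported. Anything short of that, in either upper cell, is not covered by the rule.

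**The case against.** The strongest reply is that this is a condensed article. Its data-management section refers to a full trial protocol, and laboratory grading tables are commonly kept there or in CRF guidance. That stands as far as a missing table goes. It does not answer the main point: the article introduces its severity criteria as the criteria, prints all three grades and defers nothing, and the gap between mild and moderate lies in that printed wording.

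A second reply is that the scale is meant for the symptoms and ailments that are also documented, and that it covers only drug-related events, not every test result. This narrows the point. But the article calls the objective findings AE indexes, and it offers no other scale for a drug-related event found through one of them.

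A third reply is that other safeguards exist. The investigator may withdraw a patient for medical reasons, serious AEs are addressed separately (without a definition), staff are trained in AE reporting, and a monitoring committee reviews CRFs. These stand; the 24-h rule is only the expedited route.

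Several stronger readings are tempting, and the document does not support them:

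- **That the scale grades only by tolerance.** Need for treatment also enters mild and moderate, and severe does not mention discomfort.
- **That a large symptom-free abnormality is always graded mild.** If it needs special treatment, it fails mild too.
- **That such an abnormality can never trigger 24-h reporting.** An emergency does so without symptoms.
- **That 96 patients × 3 on-treatment liver and kidney visits = 288 results measures the problem.** That figure counts scheduled tests with full attendance, not abnormal results or misgraded events.
- **That the difference between arms would be understated.** The article does not define the safety comparison by grade, and the measured values remain available for between-group analysis.

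**Conclusion.** The point holds in a limited form. Read as printed, the scale has no grade for a tolerated or symptom-free event that needs special treatment but is not an emergency. It caps a marked, untreated, symptom-free abnormality at mild whatever its size. Neither kind of event has a route to the 24-h report, and such events cannot be graded consistently in an open-label trial.

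In scope, the misfit covers all ten index groups. In frequency, its size is unknown: the article gives no expected rate of marked, symptom-free, non-emergency abnormalities, so no count of affected events can be given. No direction of bias between JTTZ and metformin is shown.

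The conclusion assumes that the printed definitions are the operative ones and that their conditions are joined as written. If the full protocol holds a separate scale for objective findings, what remains is the need to cite it and bring the two texts into line. This is a low-cost improvement to safety recording, not a threat to the efficacy analysis.

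**What to change.** 1. Reword the scale so that need for special treatment alone is enough for at least moderate, whether or not there is discomfort. While doing so, give the other empty cell (not tolerated, untreated) a grade, so that every event has one.
2. Keep the discomfort wording for symptoms. Grade the listed objective indexes on a standard published scale, by size of deviation from the reference range and from the patient's week-0 value. Table 1 marks no week-0 measurement for microalbumin, its creatinine ratio or the two ultrasounds, so those four can use the reference range only.
3. State which of those grades count as severe for the 24-h report.
4. If the full protocol already contains such a scale, cite it in the Adverse Events section and reconcile the two passages instead.

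The cost is protocol and CRF wording. No test or visit is added, because the results are already collected. The downside is that a few more events will be graded above mild and reported. The change concerns grading and reporting only and sets no treatment rule.

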### Data Management and Quality Control

To maintain high quality of the data and ensure adherence to the protocol, all investigators and research assistants were rigorously trained. The protocols for patients screening, data entry, medication use, AE reporting, and dropout recording were explained. All events will be documented on standardised CRFs. All laboratory specimens, evaluation forms, biochemical examination reports, and other records will be identified by a coded number and name only. The source medical records will be input into a professional data platform that allows for real-time data validation after being generated in each visit. The study monitoring committee (including independent data coordinators and data analysts) will perform regular data monitoring throughout the trial, review the CRFs, and ensure that information on the CRFs is consistent with that in the source medical records. The data will be independently input into the database by two research assistants. After the data are input into an electronic data platform, instant quality control and data audit procedures will be performed by the individual investigator to ensure the accuracy and reliability of these data. All study data will be managed as detailed in the full trial protocol and in accordance with the data management plan. Missing data or specific errors in the data will be sent to the investigator for a resolution. Original CRFs will be stored at the research centre for 5 years after the study completion. All the electronic data will be stored in the password-protected files on a designated computer with access restricted to the study staff. In addition, two backups will be separately stored in the Administration Office of Drug Clinical Trial in the Guang’anmen Hospital and the Clinical Evaluation Centre of the China Academy of Chinese Medical Science.

### Statistical Analysis

Intention-to-treat, per-protocol analysis, and the safety analysis will be performed. The per-protocol analysis will include only those patients who completed treatment and follow-up protocols in the allocated intervention group. Continuous variables (including age, disease duration, blood glucose, HbA1c) will be reported as means and standard deviations or as medians and interquartile ranges, as suitable. Categorical variables (including sex, past medical history, and previous treatment) will be reported as proportions. Continuous variables will be compared between the groups using analysis of variance and repeated measurement design will apply repeated-measure analysis of variance, including group and time-group interactions. The Wilcoxon rank sum test will be used to analyse non-normally distributed data. Count and grade data will be reported as frequencies (constituent ratio). Count data will be tested with the chi-square test or Fisher’s exact probability method, and grade data will be analysed using the Wilcoxon rank sum or Cochran-Mantel-Haenszel test. All statistical analyses will be performed using SPSS (version 24.0; IBM Corp., Armonk, NY, United States), and statistical significance will be set as two-sided *p*-values of ≤0.05.

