Traditional Chinese Medicine (TCM) approaches reportedly improve glycaemic control, blood lipid levels, and weight management. (Wu et al., 2020). In fact, a TCM herbal formula may ameliorate blood glucose and lipid levels by shifting the composition of the gut microbiota. (Tong et al., 2018). The Jiangtang Tiaozhi (JTTZ) recipe has been used to treat patients with T2DM with dyslipidaemia for many years. (Zhao, 2013). Interestingly, the findings from a multi-centre trial suggested that it is safe and effective in the management of the blood glucose levels, lipid levels, and weight in patients with T2DM with obesity and hyperlipidaemia. (Yu et al., 2018). The formula consists of eight Chinese herbs, including Aloe [*Aloe vera* (L.) Burm. f. or *Aloe ferox* Mill. (Asphodelaceae)], *Coptidis rhizoma* [*Coptis chinensis* Franch., *Coptis teeta* Wall., or *Coptis deltoidea* C.Y.Cheng and P.K.Hsiao (Ranunculaceae)], *Anemarrhenae rhizoma* [*Anemarrhena asphodeloides* Bunge (Asparagaceae)], red yeast rice [*Fermentum Rubrum* (Aspergillaceae)], bitter melon [*Momordica charantia* L. (Cucurbitaceae)], *Salvia miltiorrhizae radix et rhizoma* [*Salvia miltiorrhiza* Bunge (Lamiaceae) ], *Schisandrae chinensis fructus* [*Schisandra chinensis* (Turcz.) Baill. (Schisandraceae)], and *Zingiberis rhizoma* [*Zingiber officinale* Roscoe (Zingiberaceae)]. In the TCM theory, the JTTZ recipe clears the excess heat in the stomach and intestines, thus alleviating patients’ symptoms. However, the mechanism underlying the clinical efficacy of the JTTZ recipe remains unknown. We hypothesised that the JTTZ may exert a therapeutic effect equal to or better than that exerted by metformin among patients with T2DM with dyslipidaemia, and that this effect may be mediated by the modulation of metabolites secreted by the gut microbiota. Therefore, a randomised, positive drug parallel-controlled, open-label clinical trial was designed; 16S rRNA gene sequencing as well as gas chromatography/time-of-flight mass spectrometry analyses will be performed to explore these mechanisms.

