## Methods

### Study Design

This study is a randomised, positive drug parallel-controlled, open-label, non-inferiority clinical trial in patients with glucose and lipid metabolism disturbances. In total, 96 patients diagnosed with T2DM and dyslipidaemia will be recruited for this study. The patients will be randomly divided into two groups and treated with the JTTZ recipe or metformin for 12 weeks. This study protocol follows the Standard Protocol Items: Recommendations for Interventional Trials. (Chan et al., 2013). (Supplementary File S1). The study flow is illustrated in Figure 1. All information related to the treatment schedule is presented in Table 1.

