### Sample Size

Based on a previous study, the HbA1c level generally reduced by 1.0 and 0.9% using metformin and JTTZF for treatment, respectively. (Zhao, 2013; China Diabetes Society, 2021). The sample size was calculated by assuming a test power of 80% and a confidence level of 95%, Z_1-alpha/2_ = 1.960, alpha = 5% for the two-tailed hypothesis, Z_1-beta_ = 0.842, sigma = 0.024. A total of 38 patients are required in each group. Allowing for a 20% dropout rate during the follow-up period, the sample size was increased to at least 48 patients for each group, thus, creating a total sample of 96 patients. PASS software (version 11.0; NCSS, LLC. Kaysville, UT, United States) was used for these calculations.

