### Primary Outcomes

The changes of HbA1c levels are the primary study outcomes Besides, the rates of effectively regulated HbA1c, FPG, 2 h-PG, TG, and LDL-C levels will be calculated based on the number of patients who make the target achievement. The HbA1c level ≤7%, FPG level ≤7.0 mmol/L (126 mg/dl), 2 hP G level ≤10.0 mmol/L (180 mg/dl), TG level ≤1.7 mmol/L (150 mg/dl), LDL-C level ≤3.3 mmol/L (130 mg/dl) will be set as the target achievement. The FPG levels will be tested during the screening period, before intervention, and every 4 weeks during the treatment period. The levels of HbA1c, 2 h-PG, TG, and LDL-C will be recorded during the screening period, at the beginning and at the end of the12-week treatment period.

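### The trial is declared non-inferiority, but the analysis and sample size provide only for two-sided tests of no difference, with no margin, so nothing planned can support that conclusion

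*Protocol article*

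**What the plan says.** All references are to the protocol article.

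- **Objective.** Study Design calls this a "randomised, positive drug parallel-controlled, open-label, non-inferiority clinical trial". Background hypothesises that "the JTTZ may exert a therapeutic effect equal to or better than that exerted by metformin".
- **Endpoint.** Primary Outcomes states: "The changes of HbA1c levels are the primary study outcomes". Target-achievement rates for HbA1c, glucose and lipids are listed beside it.
- **Sample size.** The effect input is that "the HbA1c level generally reduced by 1.0 and 0.9% using metformin and JTTZF for treatment, respectively". The level is "alpha = 5% for the two-tailed hypothesis", with 80% power and a sigma of 0.024. The result is 38 per group, raised to 48 for 20% dropout, 96 in all. No margin is among the inputs.
- **Analysis.** "Continuous variables will be compared between the groups using analysis of variance", with repeated-measures ANOVA where it applies. HbA1c is among the continuous variables named in that section. Non-normal data go to the Wilcoxon rank sum test, and counts to chi-square or Fisher's exact test. Significance is two-sided at 0.05 throughout. Intention-to-treat and per-protocol analyses are both planned.

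**The concern.** A non-inferiority claim requires rejecting the null hypothesis that JTTZ is worse than metformin by at least a margin M. Every between-group test listed has a different null, that of no difference. Failing to reject that null is not evidence of non-inferiority, because a noisy trial fails to reject it easily. Rejecting it against JTTZ does not show inferiority by a relevant amount either, because a precise trial can detect a deficit that lies inside any reasonable margin.

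The primary conclusion is at stake. If the article is followed as it stands, the trial ends with a p-value that does not answer the declared question, and a reader may take non-significance for the answer. The trial is open-label, so a margin chosen after results by arm are known would carry little weight.

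**Working it through.** **1. Reproduce the stated sample size.** Inputs from the Sample Size section: difference 1.0 − 0.9 = 0.1, z-values 1.960 and 0.842, sigma 0.024.

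n per group = 2 × variance × (1.960 + 0.842)² / difference²

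With 0.024 read as the variance: 2 × 0.024 × 2.802² / 0.1² = 37.7, so 38. Then 38 / 0.8 = 47.5, so 48 per group and 96 in total. With 0.024 read as an SD in percentage points, the formula gives 1 per group. The stated figure therefore reproduces only with 0.024 as a variance, which implies SD = √0.024 = 0.155. This SD is inferred, not stated.

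This is the size of a two-sided difference test. On these inputs it has 80.3% power, and the difference it would detect is JTTZ doing worse than metformin.

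**2. Could 0.1 be a margin?** A non-inferiority formula with margin 0.1 and true difference 0 also gives 38, because the arithmetic is identical. The article, however, presents 0.1 as the expected difference between arms. If 0.1 were the margin and the expected deficit were also 0.1, margin minus deficit would be 0 and power would stay at 2.5% for any n.

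**3. Risk if non-significance is read as non-inferiority.** Assumed, because the article does not give them: a true JTTZ deficit of 0.4 percentage points, and the SD of the HbA1c change. For a two-sample t-test, SE = SD × √(2/n), the non-centrality is 0.4 / SE, and the risk is the probability that |t| stays below its two-sided 5% critical value. Example: SD 1.0 with n = 38 gives SE 0.229, non-centrality 1.74 and a risk of 59%.

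| SD | p>0.05, 38 per group | p>0.05, 48 per group |
|---|---|---|
| 0.155 (inferred) | about 0 | about 0 |
| 0.5 | 7% | 3% |
| 0.8 | 42% | 32% |
| 1.0 | 59% | 51% |
| 1.2 | 70% | 63% |

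A rule comparing the two-sided 95% confidence limit with a margin of 0.4 holds this error at 2.5% in every row.

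**4. The opposite case.** At the inferred SD of 0.155 with 38 per group, SE = 0.155 × √(2/38) = 0.0355. An observed deficit of 0.1 gives a 95% CI of −0.1 ± 0.07, about −0.17 to −0.03. The planned test is significant against JTTZ, yet the interval excludes a deficit of 0.2.

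**5. Power of a confidence-interval rule at the planned size.** Assumed margin 0.4, 48 per group; power = Φ((0.4 − true deficit)/SE − 1.96).

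| SD | True deficit 0 | True deficit 0.1 |
|---|---|---|
| 0.8 | 69% | 45% |
| 1.0 | 50% | 31% |
| 1.2 | 37% | 23% |

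The 0.1 column uses the Sample Size section's own expected difference.

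**The case against.** The strongest reply is that this is a condensed article. Its data-management section refers to a full trial protocol that is not shown, and a margin could be in that document or in an analysis plan. The Statistical Analysis section is a general list of methods and never singles out the primary comparison. The two-sided 5% level is also not itself at fault: the same ANOVA yields a two-sided 95% CI that would serve if its limit were compared with a margin.

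Part of this stands. A missing margin alone would not be a finding. But the article is not silent. It states the tests, the threshold and a two-tailed sample size without a margin, and none of these fits the design it declares. That mismatch is on the page.

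A reader might also infer that the plan treats a non-significant result as success, or a significant deficit as failure. The article does not say so; it sets a significance threshold and no success rule. The supportable statement is that it leaves non-significance open to being read as non-inferiority.

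The size of the risk can fairly be challenged too. The figures of 42 to 70% need an SD of 0.8 to 1.2, which the article does not give. At smaller SDs the risk shrinks, and at the inferred 0.155 it disappears.

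**Conclusion.** The point holds as an internal contradiction: the declared objective is non-inferiority, while the stated tests and sample size address a two-sided difference. If the Statistical Analysis section is followed as written, no planned analysis can support a non-inferiority conclusion. This part needs no assumption beyond the text.

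The size does rest on assumptions. For an assumed deficit of 0.4, the chance of a non-significant result runs from about 0 (SD 0.155) to 70% (SD 1.2, 38 per group), against 2.5% under a margin-based rule. These figures show what a misreading could cost; they do not describe a rule that the plan adopts. The change should be made before any data are seen by arm, because it concerns the primary conclusion.

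**What to change.** State the primary rule along these lines: *JTTZ is non-inferior if the lower limit of the two-sided 95% CI for the difference in week-12 HbA1c reduction (JTTZ minus metformin) lies above −M in both the intention-to-treat and per-protocol sets; superiority is tested only if non-inferiority is met.* Fix and justify M now, before any look at data by arm.

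Keep the difference tests for the other outcomes, including the target-achievement rates, and do not use them to claim non-inferiority.

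In the Sample Size section, restate the power that 38 completers (48 randomised) per group give for that M, the assumed true difference and an SD clearly labelled as such.

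If no margin can be defended, drop the non-inferiority label and claim only what a difference test supports.

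The text change is short and both analysis sets are already planned. The real cost is that a margin must be defended and the restated power may fall well below 80%.

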### Randomisation and Allocation

The randomisation scheme was generated by the Administration Office of Drug Clinical Trial in the Guang’anmen Hospital, using the PROC PLAN procedure in SAS statistical software (version 9.4; SAS Institute, Cary, NC, United States), with a 1:1 allocation ratio to the experimental and control groups (total sample, 96 patients). The randomisation code will be released by the interactive web response system to conceal group allocation. Eligible patients will be assigned to the interventions by research assistants, according to the unique number from the randomisation scheme, the patients will receive study treatment assigned by the scheme.

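### Continuous outcomes are compared without a baseline covariate, although week-0 values are collected for all of them; baseline adjustment would gain precision and give a clear week-12 estimate

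*Protocol article*

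**What the plan says.** The Statistical Analysis section of the protocol article sets two methods for normally distributed continuous data. The general one is: "Continuous variables will be compared between the groups using analysis of variance". For outcomes measured more than once: "repeated measurement design will apply repeated-measure analysis of variance, including group and time-group interactions". No covariate, ANCOVA or mixed model is named.

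The Primary Outcomes section makes the change in HbA1c the primary outcome. Table 1 and the outcome sections show when values are taken:

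- HbA1c, 2 h-PG and lipids: weeks 0 and 12 of the treatment period, and again at week 48.
- FPG, body weight, BMI, waist circumference and TCM symptom score: weeks 0, 4, 8 and 12.

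The Removal, Dropout, and Termination Criteria section says that dropouts enter the analysis with the last value recorded for them. The Study Design section calls the trial a non-inferiority trial.

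**The concern.** A week-0 value exists for every continuous outcome, but the stated models use it only by subtraction, or as one more time level. Entry criteria leave HbA1c unrestricted and allow FPG from 7.0 to 13.9 mmol/L, or 2 h-PG from 11.1 mmol/L with no upper limit, so baseline is likely to predict the week-12 value to some degree. A model that estimates that relationship uses the information better than one that ignores it or fixes its slope at 1.

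Two things are at stake. One is precision, in a trial sized at 38 evaluable patients per arm. The other is which number carries the conclusion. The repeated-measures model lists both a group term and a time-group term, and the article does not say which is inferential. A non-inferiority decision needs one signed difference with a confidence interval. With four visits the time-group term is a test on 3 degrees of freedom and gives no such difference by itself.

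**Working it through.** **The plan's own figure.** Inputs from the Sample Size section: "the HbA1c level generally reduced by 1.0 and 0.9% using metformin and JTTZF for treatment, respectively", so a difference of 0.1; "alpha = 5% for the two-tailed hypothesis", Z = 1.960; 80% power, Z = 0.842; sigma = 0.024. The unadjusted two-sample formula is n = 2(1.960 + 0.842)² × variance / 0.1².

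- With 0.024 read as a variance: 2 × 7.851 × 0.024 / 0.01 = 37.7, rounded up to 38. This matches "A total of 38 patients are required in each group".
- With 0.024 read as a standard deviation: 2 × 7.851 × 0.000576 / 0.01 = 0.9, or 1 per arm.

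The 20% dropout allowance gives 38 / 0.8 = 47.5, rounded up to 48 per arm and 96 in total. The meaning of sigma is a separate question. What matters here is that the calculation is an unadjusted comparison with no baseline correlation in it. The 38 sets only the scale below; the variance ratios do not depend on n.

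**Variance factors.** Let r be the correlation between week-0 and week-12 values, with equal variance s² at both times. The article gives no r, so 0.3 to 0.8 is assumed. Per patient, in units of s²:

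- week-12-only ANOVA: 1
- change score, which equals the time-group test when there are two time points: 2(1 − r)
- ANCOVA: 1 − r²
- ANCOVA relative to change score: (1 − r²) / [2(1 − r)] = (1 + r)/2

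| r | Change score | ANCOVA | ANCOVA / change | SE lower than change by | SE lower than week-12-only by | 38 per arm with change score becomes, with ANCOVA |
|---|---|---|---|---|---|---|
| 0.3 | 1.40 | 0.91 | 0.65 | 19% | 5% | 25 |
| 0.5 | 1.00 | 0.75 | 0.75 | 13% | 13% | 29 |
| 0.7 | 0.60 | 0.51 | 0.85 | 8% | 29% | 33 |
| 0.8 | 0.40 | 0.36 | 0.90 | 5% | 40% | 35 |

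The ANCOVA column is also its ratio to the week-12-only analysis, whose factor is 1. The two gains move in opposite directions as r rises, but ANCOVA is ahead of both at every r in the table. These formulas ignore the small cost of estimating the slope; the simulation below includes it.

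**Group main effect.** With weeks 0 and 12 as the two levels, the group term compares patient averages (Y0 + Y12)/2. Randomised arms have the same expected Y0, so a week-12 difference d gives (0 + d)/2 = d/2, with variance factor (1 + r)/2. The time-group term compares Y12 − Y0 and estimates d in full.

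**Power at 38 per arm.** The effect is set so that a week-12-only ANOVA has 80% power.

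| r | ANCOVA | Change / time-group | Group main effect |
|---|---|---|---|
| 0.3 | 84% | 66% | 41% |
| 0.5 | 90% | 80% | 37% |
| 0.7 | 97.5% | 95% | 33% |

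**Simulation check** (4,000 runs at each of r = 0.3, 0.5 and 0.7; 38 per arm). The mean estimate divided by the true effect was 0.99 to 1.00 for the change score and for ANCOVA, and 0.50 (0.495 to 0.498) for the group main effect. Power was 82%, 89% and 97% for ANCOVA and 65%, 79% and 95% for the change score, close to the formulas.

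**The case against.** The strongest reply is that nothing here is wrong. The primary outcome is a change score, and under randomisation an unadjusted comparison of changes is unbiased. An article may also leave covariates to a full protocol or analysis plan that is not shown. The first part stands, and it limits the point to efficiency and clarity. The second stands only in part: the article does not stay silent but names the method and the model terms, and those contain no baseline covariate. If a fuller document already adjusts for baseline, the article's wording needs only to be aligned with it.

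A second reply is that the size is assumed. That stands. No correlation is given, and if baseline predicts week 12 strongly, the gain over a change score is at its smallest: about 8% in standard error at r = 0.7 and 5% at 0.8. Also, 38 per arm is the number after allowing for dropout; 48 per arm are to be randomised.

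A reader might infer three stronger charges that the documents do not support:

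- *That the planned HbA1c estimate is halved.* The halving affects only the group main effect with week 0 as a repeated level. The article does not say that this term will be reported as the treatment effect, nor that HbA1c, with one on-treatment value in the treatment period, goes into the repeated-measures model. The change in HbA1c and the time-group term are undiluted.
- *That the analysis is complete-case and so conflicts with intention to treat.* The Removal, Dropout, and Termination Criteria section brings in each dropout's last record, and only the per-protocol set is limited to completers. SPSS would delete incomplete patients only where no value is carried forward.
- *That chance baseline imbalance goes unaddressed.* A change score does subtract baseline. Given an imbalance, it tends to over-correct through regression to the mean.

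**Conclusion.** The point holds as a gain in precision and a clearer estimate, not as a correction of bias. The stated models omit a covariate that is already collected for every continuous outcome. For assumed correlations of 0.3 to 0.8 and equal variances, adding it lowers the standard error by 19% to 5% against the change-score comparison, which is the relevant one for the primary outcome as defined, and by 5% to 40% against a week-12-only ANOVA. The group main effect with week 0 as a level should not carry the inference, because over weeks 0 and 12 it estimates half the week-12 effect.

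The direction does not depend on the equal-variance assumption. With standard deviations s0 and s12, the change-score variance exceeds the ANCOVA variance by (s0 − r·s12)², which is never negative. The exact size does depend on it, and on r.

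**What to change.** State in the Statistical Analysis section, or confirm in the fuller plan:

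- **HbA1c:** ANCOVA of the week-12 value on treatment, with week-0 HbA1c as covariate. Use the adjusted difference and its 95% CI for the non-inferiority decision. The same model suits 2 h-PG and lipids where they are analysed as continuous.
- **FPG, weight, BMI, waist circumference and TCM symptom score:** a mixed model for repeated measures on weeks 4, 8 and 12 with baseline, visit, treatment and treatment-by-visit. Report the week-12 contrast with its 95% CI.
- If repeated-measures ANOVA is kept anywhere with week 0 as a level, say that the group main effect is not the treatment estimate.

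The mixed model would also replace carry-forward of the last record for the 4-weekly outcomes, on a missing-at-random assumption. ANCOVA alone does not settle missing week-12 HbA1c. No HbA1c is scheduled between weeks 0 and 12, so the last record of a patient who leaves before week 12 is normally the baseline value, which counts as no change. That needs its own rule.

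The cost is wording only: no extra visits, samples or patients, and both models run in SPSS, the named software.
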